# The efficacy of a blended intervention to improve physical activity and protein intake for optimal physical recovery after oncological gastrointestinal and lung cancer surgery, the Optimal Physical Recovery After Hospitalization (OPRAH) trial: study protocol for a randomized controlled multicenter trial

**DOI:** 10.1186/s13063-023-07705-2

**Published:** 2023-11-27

**Keywords:** Cancer, Surgery, Supportive care, Physical functioning, Physical activity, Protein intake

## Abstract

**Background:**

Improving physical activity, especially in combination with optimizing protein intake, after surgery has a potential positive effect on recovery of physical functioning in patients after gastrointestinal and lung cancer surgery. The aim of this randomized controlled trial is to evaluate the efficacy of a blended intervention to improve physical activity and protein intake after hospital discharge on recovery of physical functioning in these patients.

**Methods:**

In this multicenter single-blinded randomized controlled trial, 161 adult patients scheduled for elective gastrointestinal or lung cancer surgery will be randomly assigned to the intervention or control group. The purpose of the Optimal Physical Recovery After Hospitalization (OPRAH) intervention is to encourage self-management of patients in their functional recovery, by using a smartphone application and corresponding accelerometer in combination with coaching by a physiotherapist and dietician during three months after hospital discharge. Study outcomes will be measured prior to surgery (baseline) and one, four, eight, and twelve weeks and six months after hospital discharge. The primary outcome is recovery in physical functioning six months after surgery, and the most important secondary outcome is physical activity. Other outcomes include lean body mass, muscle mass, protein intake, symptoms, physical performance, self-reported limitations in activities and participation, self-efficacy, hospital readmissions and adverse events.

**Discussion:**

The results of this study will demonstrate whether a blended intervention to support patients increasing their level of physical activity and protein intake after hospital discharge improves recovery in physical functioning in patients after gastrointestinal and lung cancer surgery.

**Trial registration:**

The trial has been registered at the International Clinical Trials Registry Platform at 14–10-2021 with registration number NL9793. Trial registration data are presented in Table 1.

**Supplementary Information:**

The online version contains supplementary material available at 10.1186/s13063-023-07705-2.

## Introduction

Major surgical procedures for gastrointestinal (GI) and lung cancer frequently result in significant loss of muscle mass, caused by increased catabolism due to the surgical stress response. This has major implications for postoperative physical function and has been associated with postoperative morbidity, mortality and quality of life [1–6]. Adequate physical activity and nutrition are important to prevent loss of muscle mass [7–10]. A combination of both is even more important, as adequate protein intake is needed to optimally benefit from the physical training stimuli [11]. This has also been reflected in the results from a systematic review showing that a combination of adequate protein intake and sufficient physical activity facilitates muscle gain in sarcopenia [12]. Therefore, to minimize the postoperative loss of muscle mass and restore physical function, it is important for patients with cancer undergoing surgery to maintain or enhance their physical activity and nutritional status in the postoperative phase (Table 1).

**Table 1 Tab1:** Trial registration data set

Data category	Information
Primary registry and trial identifying number	International Clinical Trials Registry Platform NL9793
Date of registration in primary registry	14 October, 2021
Secondary identifying numbers	NL78840.029.21
Source(s) of monetary or material support	Amsterdam UMC, location VUmc, department of Rehabilitation
Primary sponsor	Amsterdam UMC, location VUmc, department of Rehabilitation
Secondary sponsor(s)	Amsterdam Movement Sciences Institute
Contact for public queries	[name], [contact]
Contact for scientific queries	[name], [contact] Amsterdam UMC, location VUmc, department of Rehabilitation, Amsterdam, The Netherlands
Public title	Optimal Physical Recovery After Hospitalization (OPRAH study)
Scientific title	The efficacy of a blended intervention to improve physical activity and protein intake for optimal physical recovery after oncological gastrointestinal and lung cancer surgery: study protocol for a randomized controlled multicenter trial
Countries of recruitment	The Netherlands
Health condition(s) or problem(s) studied	Rehabilitation after oncological surgery
Intervention(s)	Intervention: Smartphone application and corresponding accelerometer in combination with coaching by a physiotherapist and dietician during three months after hospital discharge
	Control: Usual care
Key inclusion and exclusion criteria	Ages eligible for study: ≥ 18 years Sexes eligible for study: both Accepts healthy volunteers: no
	Inclusion criteria: adult patient (≥ 18 years), scheduled for curative intent surgery for gastrointestinal cancer, including esophageal and stomach cancer (upper GI), colorectal and hepato-pancreato-biliary (HPB) cancer, or lung cancer with a planned hospital stay of ≥ 2 nights, able to fill in online questionnaires in Dutch and give informed consent
	Exclusion criteria: pulmonary wedge resection, surgery with open/close procedure, having no access to a mobile device compatible for applications, less than 5 days between inclusion and surgery, patients who are wheelchair dependent, a Mini-Mental State Examination (MMSE) ≤ 24 and already participating in a conflicting study
Study type	Multicenter randomized controlled intervention trial with allocation at level of the individual
	Allocation: randomized
	Primary purpose: treatment
	Phase III trial
Date of first enrolment	June 2022
Target sample size	161
Recruitment status	Recruiting
Primary outcome(s)	Recovery in physical functioning six months after hospital discharge
Key secondary outcomes	Physical activity, lean body mass, pain, fatigue, muscle mass, protein intake, physical performance, patient-specific activity limitations, self-efficacy, participation in social roles and activities, generic quality of life, global perceived effect, hospital readmission and adverse events

However, patients often experience barriers to being physically active after surgery, e.g. due to physical symptoms, such as pain and fatigue, and lack of motivation or social support [13–16]. In addition, previous studies found that many surgical patients were unable to meet their protein requirements after surgery despite the advices of a dietician, e.g. due to a loss of appetite or feelings of worry [17]. Patients emphasize the need for more supportive care interventions after discharge to facilitate return to normal activities after cancer surgery [18, 19]. Therefore, additional support in promoting physical activity and protein intake is needed to improve recovery of physical functioning after surgery in these patients [20].

Self-monitoring of physical activity with the use of accelerometers is an often used strategy to increase physical activity in patients, by giving patients insight in their daily physical activity level [21]. A recent meta-analysis showed that interventions combining accelerometers with feedback using different behavioral change techniques (BCTs) and coaching by a health care professional are more effective in increasing physical activity than the use of an accelerometer alone [22]. In this study, it is suggested that this is due to the fact that incorporating coaching by a health professional to the intervention gives the opportunity to provide targeted advice and interventions for a specific population group with a more personal touch. Also, more BCTs can be used when a health care professional is involved, e.g. problem solving, social reward. In addition, findings of a review on patients with a colorectal adenoma indicate that behavioral interventions can encourage these patients to improve their diet [23]. The effect of a combined intervention, using eHealth and remote coaching by a dietician and physiotherapist in patients after GI or lung cancer is unknown.

We therefore developed a blended intervention to support patients in increasing their level of physical activity and protein intake after hospital discharge: The Optimal Physical Recovery After Hospitalization (OPRAH) intervention. The purpose of the OPRAH intervention is to encourage self-management of patients in their recovery in physical functioning, by using a smartphone application and corresponding accelerometer in combination with coaching by a physiotherapist and dietician. To investigate the potential effect of providing ongoing support on physical activity and protein intake after hospital discharge on recovery in physical functioning, the intervention will be compared to usual care. Therefore, the aim of this randomized controlled multicenter trial is to investigate the effectiveness of the OPRAH intervention on recovery of physical functioning, compared to usual care, in patients who have undergone elective GI and lung cancer surgery.

### Objective and hypothesis

*Objective:* to evaluate the efficacy of the OPRAH intervention on recovery of physical functioning (compared with usual care) in patients who have undergone elective GI and lung cancer surgery.

*Hypothesis*: The aim of the intervention is to encourage self-management of patients by the use of self-monitoring on physical activity and protein intake. Patients will also be monitored in their recovery of physical activity and protein intake by a physiotherapist and dietician. If this recovery stagnates and goals are not achieved, the physiotherapist or dietician can contact the patient to identify barriers in their recovery. The use of multiple BCTs can help to reduce or eliminate these barriers and to increase the patient’s level of physical activity and protein intake. Higher levels of physical activity and achieving protein requirements are expected to have a positive effect on the recovery in physical functioning after discharge. Therefore, it is hypothesized that patients in the intervention group will have a faster and better recovery in physical functioning during the first 6 months after hospital discharge compared to patients receiving usual care.

## Methods

### Study design

The proposed study is a multicenter, single-blinded two-arm randomized controlled study comparing a blended intervention delivered alongside usual care, with a control arm (usual care) in patients after hospital discharge who have undergone GI or lung cancer surgery. Baseline measurements (*T*_0_) will be conducted prior to surgery and follow-up measurements take place at hospital discharge (*T*_1_) and 1 (*T*_2_), 4 (*T*_3_), 8 (*T*_4_) and 12 (*T*_5_) weeks and 6 months (*T*_6_) after hospital discharge. The trial will be conducted at two hospitals in the Netherlands: Amsterdam UMC, location VUmc and St. Antonius, location Nieuwegein. The OPRAH trial has been designed in accordance with the Consolidated Standards of Reporting Trials (CONSORT) statement [24]. The Standard Protocol Items Recommendations for Interventional Trial (SPIRIT) checklist is provided as additional file. See Fig. 1 for the flowchart of the study and Fig. 2 for the SPIRIT schedule of enrollment, intervention and assessments.

**Fig. 1 Fig1:**
[figure not shown]
Flow chart

**Fig. 2 Fig2:**
[figure not shown]
SPIRIT schedule of enrolment, intervention, and assessments

### Participants

#### Eligibility criteria

Patients are eligible to participate when scheduled for curative intent surgery for gastrointestinal cancer, including esophageal and stomach cancer (upper GI), colorectal and hepato-pancreato-biliary (HPB) cancer, or lung cancer with a planned hospital stay of ≥ 2 nights, are aged 18 years or older, and whether they are able to fill in online questionnaires in Dutch and give informed consent.

Exclusion criteria are the following: pulmonary wedge resection, surgery with open/close procedure, having no access to a mobile device compatible for applications, less than 5 days between inclusion and surgery, patients who are wheelchair dependent, a Mini-Mental State Examination (MMSE) ≤ 24 and already participating in a conflicting study.

#### Recruitment

Potentially eligible patients will be informed about the study by the treating dietician, physiotherapist, nurse specialist or case-manager during a preoperative consultation. When the patient is interested in participation, the researcher will contact the patient after 24 h to further explain the study procedures and to answer questions of the patient. If the patient is eligible and willing to participate, the informed consent letter will be signed before the start of the baseline measurements. During the informed consent procedure, participants are also asked to confirm if their data may be used to support other research in the future. Participants will also indicate whether they would be willing to be contacted about future-related research and if they give consent to the making, use and retention of audio recordings of conversations with the dietitian and physiotherapist. In case there are doubts about the patients’ cognition, the MMSE will be administered before final inclusion. The patient receives a copy of the signed informed consent. The recruitment period is 18 months, with a target of approximately 10 included participants per month.

#### Randomization and blinding

After the baseline measurements, patients will be randomly assigned to the control or intervention group with a 1:1 allocation ratio using the randomization tool of Castor Electronic Data Capture (EDC) [25]. Randomization will be stratified per center by type of surgery (lung, HPB, upper GI, colorectal) and ASA score (1–2 or ≥ 3). The randomization tool of Castor ensures concealment of allocation. The researcher informs the participant by e-mail which group he has been assigned to. Assessments will be conducted by a blinded research assistant. Neither the patient nor the therapist will be blinded.

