### Usual care

Both participants in the intervention and the control group receive usual care.

During hospitalization, patients are treated according to the Early Recovery After Surgery (ERAS) protocol [36]. This includes early mobilization and (nutritional) intake supported by the entire (para)medical team. In the daily consultations by the medical doctor and nursing staff, attention is paid to the improvement of mobilization and intake. The amount of consultation by the physiotherapist and dietician is determined based on the clinical assessment of the physiotherapist and dietician.

After hospital discharge, there is no usual physiotherapy care. The physiotherapist may advise the patient to continue physiotherapy in primary care, based on the clinical assessment of the physiotherapist. The usual care of the dietician differs between patient groups. In Amsterdam UMC, the dietician standard schedules postoperative consultations with patients after esophagus-, stomach-, pancreas-, biliair and Hypertherme Intraperitoneale Chemotherapy (HIPEC) cancer surgery at 2 and 4 weeks and 3 and 6 months after discharge. At St. Antonius, the dietician only schedules standard postoperative consultations at 2 weeks after discharge for patients after pancreas surgery. When necessary, more consultations can be planned. Patients after hepatic, colorectal (excl. HIPEC) or lung cancer surgery receive postoperative consultations by the dietician only on indication or the dietician may advise the patient to continue dietetic treatment in primary care. All participants are permitted to engage any form of (para)medical care during the study period.

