### Statistical analysis

Missing data will be handled using longitudinal data analysis. The differences in course of recovery between groups, measured with the CAT PROMIS-PF, will be analyzed using linear mixed model analysis, with group as independent variable and the PROMIS-PF at all postoperative measurement points (*T*_1_–*T*_6_) as dependent variable, adjusting for baseline PROMIS-PF (*T*_0_). The primary analysis will be conducted based on the full analysis set according to the intention to treat method.

Descriptive statistics will be calculated for all parameters, include mean, median, standard deviation, standard error of the mean and the interquartile range. In addition, per-protocol analysis will be performed among all participants with sufficient protocol adherence (> 80%). Continuous secondary outcomes are analyzed using linear mixed model, with group as the independent variable and outcome at all postoperative measurement points as dependent variable, adjusting for baseline scores. Dichotomous outcomes are analyzed using generalized mixed model with the same multilevel structure. A mediation analyses will be performed on the longitudinal trial data to determine if the relationship between the intervention and the primary outcome (PROMIS-PF) can be explained by improvement of PA and protein intake.

Qualitative data analysis of the focus groups will be conducted following the steps of thematic analysis by two researchers.

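### The linear mixed models are stated with group and baseline only, although randomisation is stratified by centre, surgery type and ASA class; if the strata are prognostic, reported standard errors are too large and the test is conservative

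*Protocol article*

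**What the plan says.** Under Randomization and blinding, "patients will be randomly assigned to the control or intervention group with a 1:1 allocation ratio", and "Randomization will be stratified per center by type of surgery (lung, HPB, upper GI, colorectal) and ASA score", the ASA score being split into 1–2 and 3 or more. Under Study design, "The trial will be conducted at two hospitals in the Netherlands". The design therefore has 2 × 4 × 2 = 16 strata.

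Under Statistical analysis, the course of the primary outcome "will be analyzed using linear mixed model analysis, with group as independent variable". The postoperative PROMIS-PF scores enter "as dependent variable, adjusting for baseline PROMIS-PF". Continuous secondary outcomes follow the same pattern, with "outcome at all postoperative measurement points as dependent variable, adjusting for baseline scores". Dichotomous outcomes go to a generalised mixed model said to share the multilevel structure of the linear ones, which the section does not define. Centre, surgery type and ASA class are not named as terms in any model.

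**The concern.** Stratified allocation makes the arms nearly equal within each combination of centre, operation and ASA class, so differences between strata largely cancel out of the treatment comparison. A model without the strata does not know this. It leaves the between-stratum variation in the residual and builds the standard error from it. The reported standard error then exceeds the true one, the interval is wider than it need be, and the test rejects a true null less often than 5%.

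There is reason to expect prognostic strata here. The operations range from colorectal to oesophageal, pancreatic and lung resection. Baseline PROMIS-PF is taken before surgery, so it cannot carry what each operation costs the patient in function. Usual care also differs by site and operation. Amsterdam schedules dietetic visits at 2 and 4 weeks and at 3 and 6 months after several operations, whereas "At St. Antonius, the dietician only schedules standard postoperative consultations at 2 weeks after discharge for patients after pancreas surgery". None of this proves that the strata predict PROMIS-PF once baseline is in the model, but it makes it plausible. At stake is the power that the trial could have had from the same patients.

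**Working it through.** **Inputs from the protocol article (Sample size).** Effect size 0.40, two-sided alpha 0.05, power 0.80, within-subject correlation 0.6, five follow-up measurements, 67 per group (134 in total).

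**Reproducing the planned size.** The variance factor for the mean of five correlated measurements is (1 + 4 × 0.6)/5 = 0.68. Then n = 2 × ((1.96 + 0.842)/0.40)² × 0.68 = 66.7, so 67 per group. The plan's figure reproduces.

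**Assumption.** Let R² be the share of outcome variance left after baseline that the strata explain. The documents give no value, so a range from 0 to 0.20 is shown. The planned factor of 0.68 is taken as the residual variance to which R² applies.

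**Formulas.**
- Reported standard error without the strata: √(0.68 × 2/67) = 0.1425.
- True standard error under balanced stratified allocation: 0.1425 × √(1 − R²).
- Interval width, reported over correct: 1/√(1 − R²).
- True type I error without the strata: 2 × (1 − Φ(1.96/√(1 − R²))).
- Power without the strata: Φ((0.40/0.1425 − 1.96)/√(1 − R²)).
- Power with the strata: Φ(0.40/(0.1425 × √(1 − R²)) − 1.96).

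| Assumed R² | Width ratio | True type I error, strata omitted | Power, strata omitted | Power, strata included |
|---|---|---|---|---|
| 0 | 1.000 | 5.0% | 80.2% | 80.2% |
| 0.05 | 1.026 | 4.4% | 80.8% | 82.1% |
| 0.10 | 1.054 | 3.9% | 81.4% | 84.1% |
| 0.20 | 1.118 | 2.8% | 82.8% | 88.1% |

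**In patients, at R² = 0.10.** For the model without strata to reach the adjusted model's power, whose normal deviate is about 1.00, it needs 0.40/SE = 1.96 + 1.00 × √0.90 = 2.91. That gives n = 2 × 0.68 × (2.91/0.40)² ≈ 72 per group, or 144 in total. The gain is 144 − 134 = 10 completers.

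**Simulation check.** 4,000 trials per setting, 134 patients, 16 strata, and the mean of five follow-ups analysed with and without the three factors as main effects. Block size (4) and stratum shares are assumptions. At R² = 0, 0.05, 0.10 and 0.20 the width ratios were 0.998, 1.023, 1.052 and 1.116, close to the formula. With no true effect, the baseline-only model rejected in 4.9%, 4.7%, 3.8% and 3.4% of trials (Monte Carlo standard error about 0.3 points). The value at R² = 0.20 lies a little above the analytic 2.8%, which assumes perfect balance within strata.

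**Where the loss sits.** At R² = 0.10 the estimate itself varied by almost the same amount in both models: empirical standard error 0.0928 without the strata and 0.0924 with them. The correct width for the baseline-only estimate is about 2 × 1.98 × 0.0928 = 0.367. That model reported 0.388 on average; the adjusted model reported 0.369.

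**The case against.** The strongest objection is that this is a condensed article. The analysis section never says that baseline is the sole covariate, and it also names no time term or random effect, so it may not be the whole specification. That leaves open that a fuller document lists the strata. It does not dispose of the point: the article does state the independent variable and the adjustment covariate, and that stated set does not match the stated design.

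The second objection is that the size is unknown. This stands. ASA class may overlap with preoperative function, and at R² = 0 there is nothing to gain.

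Four stronger readings should be resisted:
- A reader might infer that the treatment estimate is biased or less precise. It is neither to any material degree; only its reported precision is understated.
- A reader might infer that the trial becomes underpowered or risks false positives. On the figures above, power without the strata stays at or above the planned 80%, and the error is conservative.
- A reader might take the gain at R² = 0.10 as 134/0.90 ≈ 149, or 15 completers. That compares with an unstratified trial. Against the baseline-only analysis of this stratified trial the gain is about 10.
- A reader might carry the wide-interval argument over to the dichotomous outcomes. In a generalised mixed model on the odds-ratio scale, adjustment changes the quantity estimated and need not narrow the interval. For an outcome such as 30-day readmission, events may also be too few for five more parameters.

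**Conclusion.** The point holds for the linear mixed models of the primary and continuous secondary outcomes: as stated, they leave out the factors on which randomisation is stratified. The consequence is an overstated standard error and forgone power, not invalid inference. The forgone power is 0 to about 5 points over the assumed range, and about 3 points at R² = 0.10. These sizes rest on the assumed R², on near-complete balance within strata, and on the plan's own variance factor. The direction is secure; the size is probably modest. It is a worthwhile improvement and does not threaten the trial's validity.

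**What to change.** Name centre (2 levels), type of surgery (4) and ASA class (1–2, 3 or more) as fixed main effects, beside group and baseline, in the linear mixed models for the primary and continuous secondary outcomes, and in the per-protocol analysis of the primary outcome. This adds 1 + 3 + 1 = 5 parameters. Separate terms for the 16 cells should be avoided: 134 completers over 16 cells is about 8 each, and some would be sparse. The models for dichotomous outcomes need their own decision.

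The cost is one sentence in the analysis section. The factors are already recorded for every randomised patient, and if they turn out not to be prognostic the price is negligible (simulated width ratio 0.998). Naming them in advance also removes any later choice of covariates.
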